### Formal practice

MBSR intervention will be based of some formal practices, as follows:

*Sitting meditation* consists of sitting while maintaining a composed, upright, yet not rigid posture, with head, neck and back aligned along a vertical axis, shoulders relaxed and hands in a comfortable position. This posture allows one to practice an attitude of dignity, patience, and calmness, bringing attention to the sensations emerging in the present moment without trying to fill time. For these reasons, it is necessary to dedicate time and space to the practice. The sitting meditation practice proposed in the first meetings of the MBSR pathway consists of directing attention with intention to the breath, remaining present to the sensations that accompany each inhale and exhale, without changing it. During meditation, the mind can become distracted and drift away from the object of attention; participants are asked To pay attention firmly and gently to one’s own breath, training the mind to be less reactive and more stable. This approach allows us to embrace each moment, cultivating concentrated calm, managing the mind’s resistance, and developing acceptance, patience, absence of judgment, and inner strength. It represents a training that teaches to deliberately let go of one’s thoughts, disidentifying from their content. In the course of the MBSR program, the practice of sitting meditation gradually broadens the field of attention to other objects besides the breath: sensations in various parts of the body and the body as a whole, sounds, and the process of thoughts. Recognizing thoughts as such allows us, as Kabat-Zinn (1979, 1997, 2016), to free ourselves from the distorted reality they can create, enabling us to manage our lives with greater fluidity. Similarly, dedicating time to practice daily allows us to strengthen our awareness, recognizing and accepting ourselves as we are and not as we would like to be;The *body scan* is a meditative practice that allows us to reconnect with the body, exploring it through a meticulous examination aimed at developing concentration and flexibility of attention. It is performed by lying on one’s back and systematically directing attention to various parts of the body. During the practice, participants are invited to inhabit each area of the body with full awareness, the sensations they are experiencing as well as their absence, attuning oneself as best as one can with the experience of the part of the body, which is the object of attention. The goal is to feel each part of the body and cultivate a non-judgmental, a moment-to-moment condition of awareness. Kabat-Zinn (1997) stated that the practice of body scan allows many practitioners to perceive their bodies positively; in particular, directing attention, kindness, and acceptance toward the own body becomes a valuable experience for what he describes as self-healing.The practice related to *conscious movement through yoga* consists of slowly performing and maintaining for a time a series of stretches of muscles and joints, while also continuously bringing attention to the breath and the current sensations. Kabat-Zinn (1997) describes this formal practice as an effective method to know ourselves more deeply, whatever our health conditions. During the conscious practice of yoga, there are no efforts or goals to achieve. On the contrary, this practice allows to grasp and get closer to physical and psychological limits, without having to cross or overcome them, but practicing patience with ourselves and observing the habitual way we deal with them;The *walking meditation* practice, in which attention is directed to the experience of walking in the moment and slow motion. More precisely, one chooses the place where to carry out the practice (indoors or outdoors); one defines the straight path to be followed (beginning and end); one stands still at the starting point of the path, for a few seconds, with feet parallel and apart, knees slightly flexed, arms stretched out along the sides or hands intertwined at belly level, the gaze unfocused in front of one. The invitation is to bring attention to the soles of the feet, to the physical sensations of contact with the floor, to the distribution of body weight during the steps taken, to the movement of the legs and the entire walking body, aiming at being present with each step, aimlessly, letting go of all thoughts. Being a moving practice, participants experience how the body keeps us anchored in the here-and-now through the grounding of the feet, while our mind tends to shift between the past and future. Participants are invited to practice walking meditation daily.

### Intensive meeting

The intensive meeting will include several formal meditation practices conducted and supervised continuously by the trainer. It is usually conducted between the sixth and seventh meetings or between the seventh and eighth meetings of the study. At this time, participants have been exposed to all the formal mindfulness practices; this way, they will be able to experience them in a similar way as during silent meditation retreat days. The intensive meeting will also become a time to break the rhythm of the usual routine by paying attention to the present moment. In other words, it will be an opportunity to empower the practice of mindfulness as an invitation to turn toward one’s suffering and observe more clearly the possible mental patterns that can exacerbate it. Specifically, a sequence of practices adapted to the group of participants is usually proposed, such as: sitting meditation practices focusing on breath, body, sounds, thoughts, or non-selective meditation practices; slow conscious movements to allow space for listening to one’s body and present sensations; body scan; walking meditation. Furthermore, informal meditation practices such as mindful eating will also be offered. The trainer will invite each participant to observe his or her own experience of food during lunch (which is done more slowly than usual, devoting more time to curiously observing the sensations present during the stages of tasting, chewing, swallowing).

### Evaluation tools

A battery of standardized and self-administered questionnaires will be administered through Qualtrics platform at the beginning and end of the MBSR intervention. The questionnaires will be administered to both groups in three stages: pre-intervention (T0), after 8 weeks (T1) and after 12 weeks (T2) from the beginning of the study. After the reading of the information sheet and the signing of the informed consent, participants will be asked to answer some socio-demographic and disease status questions, and then they will be asked to answer standardized and validated questionnaires designed to investigate interoceptive sensations, metacognitive and dissociative skills, sleep quality, state anxiety and depression, general well-being, and body perception. The duration of the questionnaire administration will be approximately 30–40 min.

Specifically, the questionnaires administered will be:

#### The multidimensional assessment of interoceptive awareness (MAIA)

MAIA is a self-report questionnaire that assesses eight dimensions related to interoceptive aspects of body awareness (Mehling et al., 2012). The scale includes a total of 32 items on a 6-point Likert scale, ranging from 0 (never) to 5 (always) and covers eight “distinct but related” dimensions of interoception: awareness of bodily sensations (e.g.: “I can tell where I feel good in my body”), the tendency to ignore uncomfortable bodily sensations (e.g., “I distract myself when I feel uncomfortable or fearful sensations”), the ability to have emotional reactions as a result of negative sensations (e.g., “I worry if I feel pain or uncomfortable sensations”), the ability to regulate attention regarding multiple sensations (e.g., “I can focus sensations on my body, even when there are many distractions around me”), the ability to be aware of the relationship between bodily and affective states (e.g., “I can feel changes in my body when I am happy”), the ability to pay attention to bodily states to regulate psychological distress (e.g., “I can use my breath to help me stay calm and relaxed), the ability to feel one’s bodily sensations to make decisions (e.g., “I listen to my body to help me choose what to do”), and the experience of one’s body as safe and trustworthy (e.g., “I feel that my body is a safe place). Some subscales measure direct experience with the body, others are associated with the assessment of cognitive processes, such as self-regulation (Ferentzi et al., 2020). The total score is calculated between 0 and 160 (Valenzuela-Moguillansky and Reyes-Reyes, 2015) and the reliability for the eight subscales (Mehling et al., 2012) is between 0.66 and 0.87.

#### The Italian version of the metacognitions questionnaire (MCQ-30)

MCQ-30 is a questionnaire with 30 items distributed on a 5-point Likert scale (from “not at all agree” to “completely agree”) (Quattropani et al., 2014). It measures dysfunctional metacognition processes regarding vulnerability and maintenance of emotional disorders through five categories: (1) positive beliefs regarding worry, describing the positive evaluation of worry as being functional for planning and solving problems (6 items, e.g., “I need to worry in order to work better”); (2) negative beliefs regarding uncontrollable and dangerous aspects, assessing the negative interpretation of worry due to thoughts considered uncontrolled (6 items, e.g.: “When I start worrying, I cannot stop”); (3) cognitive confidence, in order to explore concerns related to the effectiveness of one’s memory (6 items, e.g., “I do not trust my memory”); (4) the need to control thoughts, which assesses the belief that some thoughts need to be controlled and suppressed (6 items, e.g., “I should keep my thoughts under control all the time”); (5) cognitive self-awareness, which assesses the tendency to constantly pay attention to one’s thought processes (6 items, e.g., “I am constantly aware of my thoughts”). MCQ-30 shows good psychometric properties with reference to satisfactory internal consistency, convergent validity, and good test–retest reliability (Laghi et al., 2020).

#### Dissociative experiences scale (DES)

DES is a self-report questionnaire composed of 28 items that measures the likelihood of having dissociative thinking and post-traumatic stress disorder (PTSD) (Bernstein and Putnam, 1986). Measured on a 10-point scale (from “never” to “always”), each item describes a type of experience that each subject might have had. Studies show that subjects with scores above 15 need more exploration as they are often linked to dissociative diagnoses; a score of 30 suggests a good possibility of dissociative thinking and PTSD; finally, scores above 40 indicate high likelihood of a dissociative identity disorder (Kianpoor et al., 2012). Factor analysis reports three factorial structures (Burch, 1995) that include depersonalization and derealization (e.g., feeling that our body does not belong to us), amnestic dissociation (e.g., finding new objects that one does not remember buying), and imaginal involvement (e.g., being in a familiar environment but recognizing it as strange) (Renard et al., 2012). In reference to psychometric properties, Frischholz et al. (1992) report good concurrent and criterion validity, while Olsen and Beck (2012) show high internal consistency scores with Cronbach’s alpha of 0.7.

#### The Pittsburgh sleep quality index (PSQI)

PSQI is a self-administered questionnaire that measures sleep quality and quantity in 1 month (Buysse et al., 1989). The test consists of 19 items that address seven components; specifically: subjective quality and latency of sleep, duration, usual sleep efficiency, sleep disturbances, use of appropriate sleep medications, and schedules referred to sleep dysfunctionality. There are also five additional questions completed by the partner of the participant subject, but which are not then calculated in the final scoring. The Global Sleep Quality scale reports Cronbach’s alpha of 0.83. Furthermore, a Global Sleep Quality score greater than five discriminates between good and poor sleepers with a diagnostic sensitivity of 89.6 percent and specificity of 86.5 percent (Buysse et al., 1991). Finally, the literature evidences the reliability and validity of the PSQI in different populations (Beck et al., 2004).

#### Hospital and anxiety depression scale (HADS)

HADS is a 14-item compost questionnaire on a 4-point Likert scale (0–3) to measure emotional distress (e.g., anxiety and depression) in a patient population without psychiatric symptoms (Zigmond and Snaith, 1983). The total score (0–42) results from the sum of the scores obtained in each of the two individual subscales; the first subscale is about anxiety symptoms (7 items), while the second one regards depressive symptoms (7 items) (Zigmond and Snaith, 1983). The higher the score obtained, the higher the values found in reference to anxiety and depression; values with scores of 10 and above indicate the need for clinical intervention (Zilliacus et al., 2011; LoMartire et al., 2020). Studies designed to measure the applicability of this test to different populations (Bjelland et al., 2002; Cosco et al., 2012; Norton et al., 2013) show good reliability (Bjelland et al., 2002; Zigmond and Snaith, 1983) in both the general population and in samples of patients with chronic diseases (Lynch et al., 2011; Woolrich et al., 2006).

#### Functional assessment of cancer therapy—breast cancer (FACT-B), version 4

The FACT-B is a self-administered scale comprising 36 items designed to assess Quality of Life (27 items) (Cella et al., 1993; Di Bella et al., 2018) and specific aspects related to breast cancer, including body image and sexual satisfaction (9 items) (Bichoo et al., 2021). It evaluates different domains of Quality of Life, such as physical, emotional, and relational aspects. Participants rate their level of agreement on a 5-point Likert scale (ranging from “not at all” to “very much”) based on their experiences over the past 7 days. Higher scores indicate a better Quality of Life across all the domains explored (Deepa et al., 2020).

#### Objectified body consciousness scale (I-OBCS)

I-OBCS is a questionnaire consisting of 24 items from the original English version by McKinley and Hyde (1996). Participants are asked to indicate their degree of agreement on a 7-point Likert scale (from 1: very disagree to 7: very agree). I-OBCS measures surveillance attitudes toward the body, control beliefs about one’s physical appearance, and body shame (Boursier et al., 2020). Dakanalis et al. (2017) report good construct validity, high internal consistency, and test–retest reliability.

## Data analysis and sample size

The sample size required for the present study was calculated using G∗Power 3.1.9.2 software (Faul et al., 2007), for an analysis of variance with repeated measures (ANOVA) with interaction. The primary endpoint will be the difference between the two experimental groups (i.e., between-subjects factor) in the improvement of the overall MAIA scale score at pre-intervention (T0), post-intervention (T1), and follow-up (T2) times. To detect a weak-median effect size (i.e., partial η2 = 0.04), the required sample size is 40 (i.e., 20 participants in each experimental group). The type I error rate (*α*) was set at 0.05 (two-sided) and the power (1 - *β*) was set at 0.90. The collected data will be analyzed using the statistical analysis software Statistical Package for Social Science (SPSS, version 27.0).

Adherence to the intervention will be monitored and reported in the results, and data from participants who do not adhere will be managed using an intention-to-treat analysis.

The data collected in this study will be analyzed using repeated measures ANOVA to compare the outcomes between the experimental and control groups across the three time points. The primary analysis will focus on changes in the overall MAIA scale scores, allowing us to evaluate the main effects of time and group as well as the interaction between these factors. Secondary exploratory analyses will include repeated measures ANOVAs on the individual MAIA subscales and additional psychological outcomes such as anxiety, depression, and body image perception. Effect sizes and confidence intervals will be reported alongside *p*-values to offer a comprehensive understanding of the observed effects.

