## Disadvantages or undesirable effects

No inconveniences or undesirable effects are expected for research participants. It will be the responsibility of the researchers to inform on the first presentation sheet of the study the possibilitỳ for participants to discontinue participation in the research at any time, without having to give any explanation and without incurring any possible negative consequences.

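### Intention-to-treat is promised for non-adherers, but the repeated-measures ANOVA fixed beside it normally excludes anyone missing T1 or T2

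*Protocol article*

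**What the plan says.** All the analysis statements are in the protocol article, section Data analysis and sample size.

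- **Principle.** Adherence will be monitored, and "data from participants who do not adhere will be managed using an intention-to-treat analysis".
- **Method.** "The data collected in this study will be analyzed using repeated measures ANOVA to compare the outcomes between the experimental and control groups". The comparison covers T0, T1 and T2 and is run in SPSS 27.0. The same method is named for the secondary outcomes.
- **Primary endpoint.** The group difference "in the improvement of the overall MAIA scale score at pre-intervention (T0), post-intervention (T1), and follow-up (T2) times".
- **Schedule.** Under Evaluation tools, both groups complete the questionnaires at "pre-intervention (T0), after 8 weeks (T1) and after 12 weeks (T2) from the beginning of the study".
- **Withdrawal.** Under Disadvantages or undesirable effects, participants may "discontinue participation in the research at any time".
- **Numbers.** Methods enrols 40, which equals the 40 that the sample-size paragraph requires.

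The article names no imputation, no mixed model and no other way of keeping a woman whose T1 or T2 is missing.

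**The concern.** Standard repeated-measures ANOVA (the SPSS GLM procedure) reads one row per participant and needs every time point in that row. A woman with T0 and T1 but no T2 is left out, and her two observed scores go with her. Intention-to-treat means analysing women as randomised, so principle and method part company as soon as an outcome is missing.

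Missing outcomes are foreseeable. The MBSR arm has eight weekly sessions, a meeting of about 5 hours and about 40 minutes of daily practice; the waitlist arm has no sessions before week 12. Loss linked to the burden of the course would therefore fall mainly on one arm. Whether it occurs, and how often, is a judgement and not something the article states.

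Two things are at stake. Precision suffers, because enrolment has no reserve above the required 40. The comparison also suffers, because the women left in the analysis may differ between arms in ways that randomisation no longer balances.

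**Working it through.** **1. Inputs from the article.** Two groups (k = 2), three times (m = 3), N = 40, alpha 0.05, power 0.90, partial eta squared 0.04. Hence f² = 0.04/0.96 = 0.0417 and f = 0.204.

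**2. Inputs that the article does not give.** The correlation among repeated measures (rho), the sphericity correction (taken as epsilon = 1) and the dropout rate are assumptions here.

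**3. Formula.** For the group-by-time interaction, the noncentral F has lambda = N × f² × m / (1 − rho), df1 = (k − 1)(m − 1) = 2 and df2 = (N − k)(m − 1).

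**4. The plan's own figure.** At N = 40 and rho = 0.5, lambda = 40 × 0.0417 × 3 / 0.5 = 10.0 with df2 = 76, and power is 0.80; 90% power would need N = 54. N = 40 gives 0.90 if rho is about 0.62. As rho is not stated, 40 is neither confirmed nor shown to be wrong. Both values are carried forward, and the present point does not depend on which applies.

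**5. Complete cases under two assumed patterns.**

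- The same 10% miss both follow-ups: 40 × 0.90 = 36 remain.
- 10% are missing independently at each follow-up: 0.9² = 0.81, so 19% are lost and 40 × 0.81 = 32.4, about 32, remain.

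**6. Power with those complete cases.**

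| Complete cases | df2 | rho = 0.5 | rho = 0.62 |
|---|---|---|---|
| 40 | 76 | 0.80 | 0.90 |
| 36 | 68 | 0.75 | 0.86 |
| 32 | 60 | 0.69 | 0.82 |

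The first pattern suits women who leave the course and stop responding; the second suits sporadic non-response. At the same 10% rate, the second costs about twice as many participants.

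**7. What a mixed model can and cannot recover.** Suppose the MBSR arm gains d at T1 and holds it at T2 while controls stay flat. The interaction then has f² = d²/18, so d = √(18 × 0.0417) = 0.87 SD (0.866 before rounding). Suppose also that 20% of the MBSR arm gain nothing and give neither T1 nor T2. The effect in all randomised women is 0.8 × 0.866 = 0.69 SD, and the complete-case analysis estimates 0.87 SD. A simulation of a model with T0 as covariate also gave 0.87 SD. Treating T0 as an outcome does not change this: these women then contribute only a baseline score, which in this scenario says nothing about their lack of gain. Imputing their follow-up from the flat control arm returns 0.8 × 0.866 + 0.2 × 0 = 0.69 SD.

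**The case against.** The strongest reply is that the article does not contradict itself on its face. The intention-to-treat sentence is about adherence to the intervention. A woman who skips sessions or homework but returns all three questionnaires stays in her allocated group under ANOVA, exactly as the principle requires. The questionnaires are online and timed by study week for both groups, so they do not depend on attendance. The article never mentions a complete-case rule, imputation before the ANOVA would be compatible with its wording, and a condensed article commonly leaves missing-data handling to fuller documents.

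Much of this stands. A reader might infer that the planned analysis is a completers' analysis, or that it is biased towards MBSR by a known amount. The documents support neither: the conflict arises only when outcomes are missing, no dropout rate is given, and nothing in the article shows that women who leave the course will also skip the questionnaires. The 0.87 against 0.69 SD comparison illustrates one assumed scenario; it does not estimate this trial's bias.

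The appeal to an unseen plan stands only in part. The article itself fixes the principle, the model and the software. The point concerns how those three fit together, and it does not fault the article for leaving out detail.

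**Conclusion.** The point holds in a conditional form. Followed as written, the plan delivers intention-to-treat only if every randomised woman completes T0, T1 and T2; otherwise the standard procedure removes her and her observed values. Under the assumed 10% patterns, 36 or about 32 of 40 remain. Power then falls from 0.80 to 0.75 or 0.69 at correlation 0.5, and from 0.90 to 0.86 or 0.82 at correlation 0.62. These figures rest on assumed dropout, assumed correlation and sphericity.

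A reader might also infer that a mixed model would remove any bias from selective dropout. It would not. It keeps partly observed women and is valid under missing at random, but step 7 of the working shows that it leaves bias from outcome-dependent dropout untouched.

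Severity: should-fix, not must-fix.

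**What to change.** 1. **Primary analysis.** Replace the repeated-measures ANOVA by a linear mixed model for repeated measures (SPSS MIXED). Enter T0, T1 and T2 all as outcomes, constrain the baseline means to be equal between groups (time effects plus group differences at T1 and T2 only), and use an unstructured covariance. Every randomised woman with any value is then kept in her allocated group. A joint test of the two group differences replaces the interaction test, and sphericity is no longer assumed. Entering T0 only as a covariate would lose a woman with neither follow-up. Apply the same model to the secondary outcomes.
2. **Data collection.** State that T1 and T2 questionnaires will still be sent to women who stop attending, unless they have withdrawn from the research itself.
3. **Sensitivity analysis.** Impute missing MBSR-arm follow-up values from the control arm, to show how far the result depends on missing at random.
4. **Wording.** Say that intention-to-treat covers missing outcomes as well as non-adherence.

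The cost is a change of analysis text and slightly more analysis work in the software already named. The mixed model does not restore information from women who give no follow-up, so the second item matters as much as the first.

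### The primary repeated-measures ANOVA treats baseline MAIA as an outcome level and does not name the test that decides; one baseline-adjusted contrast should be prespecified

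*Protocol article*

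**What the plan says.** All the wording below is in the Protocol article, mostly in the section Data analysis and sample size.

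- Endpoint: "The primary endpoint will be the difference between the two experimental groups (i.e., between-subjects factor) in the improvement of the overall MAIA scale score". All three visits, baseline included, are attached to this endpoint. The Evaluation tools section places them at "pre-intervention (T0), after 8 weeks (T1) and after 12 weeks (T2) from the beginning of the study".
- Sample size: calculated "for an analysis of variance with repeated measures (ANOVA) with interaction". The result is: "To detect a weak-median effect size (i.e., partial η2 = 0.04), the required sample size is 40". The type I error is 0.05, called two-sided, and the target power is 0.90.
- Analysis: "repeated measures ANOVA to compare the outcomes between the experimental and control groups across the three time points". The primary analysis concentrates on total MAIA, "allowing us to evaluate the main effects of time and group as well as the interaction between these factors".

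T0 therefore enters the model as an outcome level and not as a covariate. Three F tests stand under the primary analysis. No sentence says which one decides, and no time point or single contrast is chosen.

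**The concern.** The three F tests answer different questions.

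- The time main effect pools both arms and carries no information about MBSR against waitlist.
- The group main effect averages in T0, where randomisation makes the expected difference zero. A constant effect at T1 and T2 is thereby diluted by one third.
- The interaction is the test of differential change, but with 2 df it does not say at which visit or in which direction the groups differ.

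Two things are at stake. First, the trial has only 40 participants, and the T0 score, which is collected anyway, could sharpen the comparison as a covariate. Second, the article promises effect sizes and confidence intervals, but an omnibus 2-df test has no single estimate for them to describe. If the deciding quantity is not named in advance, the choice may be made after the results are known.

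**Working it through.** **Inputs from the article.** N = 40 (20 per arm), m = 3 visits, partial η² = 0.04, α = 0.05, target power 0.90.

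**Assumed, because the article does not give them.** A common correlation ρ between visits (range 0.3 to 0.7), equal variances, and the pattern of the effect over time.

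**1. The plan's own figure.** For the interaction, f² = 0.04/0.96 = 0.0417 and λ = f²·N·m/(1−ρ), with 2 and 2(N−2) = 76 df. At ρ = 0.5, λ = 0.0417 × 40 × 3/0.5 = 10.0 and power is 0.80; power of 0.90 would need N = 54. N = 40 gives 0.90 at ρ of about 0.62. The unstated correlation is a separate matter, and the present point does not depend on it.

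**2. An effect in SD units that matches η² = 0.04.** Take a group difference of (0, d, d) at T0, T1 and T2. The interaction effects have f² = d²/18, so d² = 18 × 0.0417 = 0.75 and d = 0.87 SD. The pattern (0, d, 0) gives the same f² and the same d, so the plan's η² does not distinguish a sustained effect from one seen at a single visit.

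**3. Variance of each estimated group difference, in SD² units (4/N = 0.1), at ρ = 0.5.**

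- Group main effect: (1+2ρ)/3 × 0.1 = 0.0667, with expected value 2d/3 = 0.577. Noncentrality 0.577/0.258 = 2.24.
- T1 adjusted for T0: (1−ρ²) × 0.1 = 0.075. Noncentrality 0.866/0.274 = 3.16.
- T1/T2 mean adjusted for T0: [(1+ρ)/2 − ρ²] × 0.1 = 0.05. Noncentrality 0.866/0.224 = 3.87.

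Power from the noncentral t (38 df for the group effect, 37 df for the adjusted contrasts), for an equal effect at T1 and T2:

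| Test | ρ = 0.3 | 0.5 | 0.62 | 0.7 |
|---|---|---|---|---|
| Group main effect | 0.68 | 0.59 | 0.54 | 0.51 |
| Interaction, 2 df | 0.65 | 0.80 | 0.90 | 0.96 |
| T1 adjusted for T0 | 0.80 | 0.87 | 0.93 | 0.96 |
| T1/T2 mean adjusted for T0 | 0.95 | 0.965 | 0.98 | 0.99 |

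Simulation with 20,000 trials per scenario agrees to within about 0.01.

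**4. Effect at one visit only (0, d, 0).** The interaction keeps 0.80 at ρ = 0.5 and 0.90 at ρ = 0.62. The adjusted T1/T2 mean now estimates d/2 = 0.433. Its noncentrality is 0.433/0.224 = 1.94, and its power is 0.47 at ρ = 0.5 and 0.53 at ρ = 0.62. Adjusted T1 keeps 0.87 at ρ = 0.5 if T1 is the visit with the effect. A joint 2-df test of T1 and T2, adjusted for T0, has 0.83 for this pattern and 0.92 for the equal effect, against 0.80 for the interaction in both.

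**5. Error rates.** With no treatment effect the interaction is significant in about 5% of trials. If any of the three F tests could count as success, the chance is 1 − 0.95³ = 0.143 (0.14 to 0.15 by simulation). If both arms drift by 0.3 SD (assumed) and ρ = 0.5, λ for time is 40 × 0.06/0.5 = 4.8, and the time test is significant in about 47% of trials.

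**The case against.** The strongest reply is that the deciding test can be identified. A between-group difference in improvement is the group×time interaction, and the sample size is for an ANOVA with interaction. The mention of the between-subjects factor can be read as a label for group, not as the choice of the group main effect. The sentence listing three effects describes what such an ANOVA produces; it is not a success rule. This stands.

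A reader might infer that the plan lets a shared improvement over time be reported as benefit, or that its type I error is 14%. The document does not support either. Both that 14% and the 47% for drift need a rule under which a test other than the interaction may be cited as success, and no such rule is written. Citing the time effect would contradict the stated endpoint.

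A reader might also infer that the ANOVA is wrong or always wastes power. It is not wrong: with randomised groups the interaction is a valid test of differential change. The power gain depends on the effect pattern and the correlation. Adjusted T1 has no real advantage over the interaction at ρ = 0.7, and the averaged contrast is clearly worse than the interaction when the effect is at one visit only.

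Finally, a condensed article may leave follow-up contrasts and covariates to a fuller document. That is fair for the details. But the article itself fixes the model, with T0 as an outcome level, and lists the tests of the primary analysis, so the comment concerns what it states.

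**Conclusion.** The point holds as a matter of clarity and efficiency. The endpoint and sample-size wording point to group×time, but the analysis text does not make it the deciding test and places two main effects beside it. The interaction is valid and keeps its 5% error, yet it yields no single directional estimate.

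Adjusting for T0 is a nearly free improvement. At N = 40 and an assumed ρ of 0.5, with an assumed equal 0.87 SD effect at T1 and T2, power rises from 0.80 to 0.87 (adjusted T1) or 0.965 (adjusted T1/T2 mean). These figures also assume equal variances and a common correlation, none of which the article states. The choice of contrast matters as much as the adjustment, and it should follow from the effect pattern the investigators expect.

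**What to change.** Rewrite the primary analysis to do the following.

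1. Model total MAIA at T1 and T2 with group, time and group×time, and with T0 MAIA as a covariate.
2. Prespecify one between-group contrast as primary, with two-sided α of 0.05 and a 95% CI: the adjusted difference at one stated time point, or the T1/T2 average if a sustained effect is expected. Report the remaining time-specific differences as secondary.
3. If the ANOVA is also reported, state that its time and group main effects are descriptive and not evidence of efficacy.

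If the investigators do not want to commit to a pattern, a joint 2-df test of T1 and T2 adjusted for T0 protects against either, but it again gives no single estimate.

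Cost: a change of wording and about one degree of freedom, with the same participants, questionnaires and software. The real risk is choosing the average when the effect appears at only one visit (power 0.47 against 0.80 at ρ = 0.5), so the reason for the chosen contrast should be written down before the data are seen.
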